### 11.4.4 Other Efficacy Variables

Other variables (visual field [other than GVF], color vision, dynamic pupillometry, nystagmus testing, OCT, and FAF) will be summarized by gene mutation subgroup, disease

cohort, and visit using mean, standard deviation, median, minimum, and maximum for continuous variables; and counts and percentages for categorical variables.

### **11.5 Safety Variables and Analyses**

Safety analyses will be performed on all subjects who received treatment (safety data set). This study has the following safety variables:

- Adverse events (AEs)
- Concomitant medications
- Vital signs (temperature, blood pressure, heart rate, respiratory rate)
- Clinical laboratory tests (including hematology, chemistry, urinalysis, thyroid function, serum retinol, and coagulation testing)
- Electrocardiogram (ECG) measurements
- Height
- Biomicroscopy, IOP, and dilated fundus exam
- BCVA score

AEs will be coded using the Medical Dictionary for Regulatory Activities (MedDRA) with the number and percentage of subjects experiencing an AE and the total number of events summarized with system organ class and preferred term. Concomitant medications will be coded with the World Health Organization Drug Dictionary (WHO DD) and tabulated. Other safety variables including clinical laboratory test results and vital signs will be summarized with appropriate descriptive statistics. ECG, biomicroscopy, IOP, dilated fundus exam, and cycloplegic refraction results will be listed by subject. See [Section 9.5](#) for details on the visual acuity score.

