See [Section 9](#) for details on study follow-up procedures and [Section 10.5](#) for details on follow-up for AEs. The Investigator should review the follow-up procedures with the subject and his/her parent(s)/guardian(s) if applicable, including the number of visits, the specific procedures to be done, and the total length of the follow-up period. The Investigator must also ensure it is understood that the subject's medical records will continue to be available for the follow-up period as described in the approved informed consent form for the entire study period.

If a subject refuses to undergo the study follow-up procedures, or his/her parent(s)/guardian(s) refuses to allow the subject to undergo the procedures, the reason for refusal should be fully documented. Subjects who do not continue study procedures should undergo all end-of-study assessments.

Subjects who miss study drug doses will continue to be followed up in the study. Additional subjects may be enrolled to replace subjects who withdraw before completing adequate study follow-up or to supplement data if several subjects miss doses of study drug.

Subjects will withdraw from the study follow-up procedures on Day 30 or at a subsequent visit, and be considered to have completed the study, if they meet entry criteria and are enrolled in a subsequent retreatment study (see [Section 1](#)).

The Sponsor may stop the study at any time.

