## 9.3 Treatment and Follow-up Procedures

Treatment and follow-up procedures will be done as identified in [Table 3](#).

On Day 0, each subject will receive the first dose of study drug. Treatment will be administered for 7 consecutive days (Day 0 to Day 6, inclusive).

Subjects will have follow-up visits on Days 7/8, 14/15 and 30; and Months 2, 4, 6, 8, 10, and 12. All visual function and safety assessments will be done on Day 7/8 (24/48 hours after taking the last dose of study drug). Visual function tests and safety assessments will be done on Day 14/15 and each subsequent visit. Women and girls of child-bearing potential will have urine pregnancy tests on Day 14/15, Day 30, and Month 2. AEs and concomitant medications will be monitored at every visit. The subject questionnaire will be completed on Day 14/15 and every subsequent visit. These procedures are described further in [Sections 9.4, 9.5, 9.6, and 9.7](#).

All efforts will be made for subjects to comply with the follow-up visit schedule. However, if the schedule is not feasible for a subject, follow-up visits will be conducted as closely to the schedule as possible.

Subjects will complete the study at the Day 30 visit, or any subsequent visit, if they meet entry criteria and are enrolled into a subsequent retreatment study (see [Section 1](#)).

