## **10 EVALUATION, RECORDING, AND REPORTING OF ADVERSE EVENTS**

All adverse events (AEs) either observed by the Investigator or one of his/her medical collaborators, or reported by the subject spontaneously, or in response to the direct question below, will be noted in the AEs section of the subject's CRF and in the source document. Only treatment-emergent AEs (those occurring during or after the start of study treatment) should be recorded as AEs. Events reported before the initial study treatment should be recorded as medical history.

In an attempt to optimize consistency of AE reporting across centers, the subject must be asked a standard question to elicit any AEs. At each clinic or telephone evaluation of the subject, study personnel will ask the following question: "Have you had any problems since your last visit or telephone call?"

If any AE is reported, the date of onset, intensity, relationship to study medication or treatment, date of resolution (or the fact that it is still continuing or has become chronic), and whether the AE is serious or not will be recorded (see [Section 10.2](#)).

For any change in laboratory results, vital signs, or ECG measurements that arises after treatment, the Investigator will decide if the value is clinically significant. The Investigator

will determine if it is necessary to repeat the evaluation. If the evaluation is judged to be clinically significant, it must be recorded as an AE.

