#### **10.5 Follow-up for Adverse Events**

Throughout the study to the final study visit, all AEs will be followed until they resolve or become chronic (as judged by the Investigator).

At the final study visit, new AEs, as well as follow-up information for continuing AEs, will be recorded in the CRF and source document. If an SAE (defined in [Section 10.1.2](#)) is unresolved at the final study visit, it will be followed by the Investigator until it resolves or becomes chronic (as judged by the Investigator). Follow-up data for such SAEs will be recorded in the source document and reported to the safety contacts (refer to [Section 10.3](#)). Non-serious ongoing AEs will be followed beyond the final study visit at the discretion of the Investigator and recorded in the source documents.

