#### **11.2.2 Safety**

The safety data set will include data from all enrolled subjects who receive any treatment. In the safety analysis, no data exclusion is allowed because of protocol violations.

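### Crude AE percentages over follow-up that ends anywhere from Day 30 to Month 12 make the rates of late-onset and background events depend on how many subjects leave for retreatment

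*Protocol*

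**What the plan says.** Five provisions of the protocol act together here.

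- **Statistic (Section 11.5, repeated in the Protocol Summary).** AEs are tabulated "with the number and percentage of subjects experiencing an AE and the total number of events summarized with system organ class and preferred term". No time window or person-time denominator is given.
- **Denominator (Section 11.2.2).** "The safety data set will include data from all enrolled subjects who receive any treatment".
- **Start of recording (Section 10).** "Only treatment-emergent AEs (those occurring during or after the start of study treatment) should be recorded as AEs". The treatment-emergent period has no stated end.
- **End of recording (Section 10.5).** "At the final study visit, new AEs, as well as follow-up information for continuing AEs, will be recorded in the CRF and source document".
- **Length of follow-up (Sections 9.3 and 5.4).** The schedule is: "Subjects will have follow-up visits on Days 7/8, 14/15 and 30; and Months 2, 4, 6, 8, 10, and 12". Retreatment cuts it short: "Subjects will withdraw from the study follow-up procedures on Day 30 or at a subsequent visit, and be considered to have completed the study", provided that they meet the entry criteria and are enrolled in the retreatment study.

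Section 4.2 describes follow-up differently, as lasting at least 12 months after treatment, with no exception for retreatment.

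**The concern.** Safety of a 7-day course is one of the three objectives in Section 3, and Section 4.2 confirms that there is no control group from which a background rate could be read. A crude percentage of treated subjects is easy to interpret when everyone is observed for about the same time. Here one completer may contribute a month and another a year.

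The chance of recording a late or unrelated event grows with time observed, so the percentage falls as more subjects move to retreatment, even if the drug does exactly the same thing. Exit also depends on meeting retreatment entry criteria, so it need not be random. A reader who relies on Section 4.2 would take the figure for a 12-month incidence, which it would not be. The total number of events has the same weakness, since it is given without the time over which the events arose.

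**Working it through.** **The plan's own figures.** The protocol states no expected AE rate, precision or retreatment share, so there is no safety figure to reproduce. The only derived number is the sample size, and it checks: 2 diseases x 2 genotypes x 7 = 28.

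**Spread of follow-up.** Day 30 is 30/30.4375 = 0.986 months. Month 12 against Day 30 is 365.25/30 = 12.2-fold. With the visit windows in Table 3 (±4 days and ±2 weeks), the ratio runs from (365.25 - 14)/34 = 10.3 to (365.25 + 14)/26 = 14.6.

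**Late-onset or background events.** Assume a constant rate λ per subject-month and a share f leaving at Day 30, with the rest followed to Month 12. The protocol gives neither value. The expected crude percentage is

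f x [1 - exp(-0.986λ)] + (1 - f) x [1 - exp(-12λ)].

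| λ per month (assumed) | none leave at Day 30 | half leave | all leave |
|---|---|---|---|
| 0.02 | 21.3% | 11.6% | 2.0% |
| 0.05 | 45.1% | 25.0% | 4.8% |
| 0.10 | 69.9% | 39.6% | 9.4% |
| 0.20 | 90.9% | 54.4% | 17.9% |

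The gap between none and all leaving is 19 to 73 percentage points. At λ = 0.05 and 28 subjects, the expected number with the event is 28 x 0.451 = 12.6 or 28 x 0.048 = 1.3. The expected event count is 28 x 0.05 x 12 = 16.8 or 28 x 0.05 x 0.986 = 1.4.

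**Any AE.** Add an acute risk p around dosing, common to all subjects. At follow-up of T months the expected figure is 1 - (1 - p) x exp(-λT).

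- p = 0.3, λ = 0.05: 33.4% at Day 30, 61.6% at Month 12.
- p = 0.6, λ = 0.05: 61.9% and 78.0%.
- p = 0.9, λ = 0.05: 90.5% and 94.5%.
- p = 0.9, λ = 0.2: 1 - 0.1 x exp(-0.197) = 91.8% and 1 - 0.1 x exp(-2.4) = 99.1%.
- p = 1: no difference.

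**Which p is plausible.** Section 1.5 reports drug-related headache in all 5 healthy volunteers at the dose used here. The exact two-sided 95% lower limit for 5 of 5 is 0.025^(1/5) = 48%. The same section places those drug-related events in the first 4 days of dosing, well before any Day 30 exit.

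**After the change.** A common window to Day 30 gives the right-hand column of the table whatever f is. Events per subject-month recover λ, provided that exit is unrelated to AE risk.

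**The case against.** The strongest reply is that onset windows and person-time rates normally belong in the SAP, which is not at hand. Section 11.5 does not say that its table is the only one. That is fair, and the absence of a window would not by itself be a finding. But the protocol fixes the statistic, the denominator, the open-ended definition and the exit rule, and followed as written these give a rate that moves with retreatment uptake.

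A second reply is that drug effects can be separated anyway. Section 10 requires onset date and relationship for each AE, and Section 10.2.2 defines the relationship categories. This stands as far as data collection goes, but Section 11.5 plans no table by relationship or by onset.

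A third is that long AE collection is deliberate. Section 8.1 notes that liver and bone effects of vitamin A toxicity reverse less predictably, and Section 9.4.5 measures height at the last visit in subjects up to 19 years. This also stands, and is why the all-period summary should be kept.

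Several stronger readings are tempting but are not supported:

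- **Leavers are scored event-free after Day 30.** No section says so. It is the arithmetic effect of a crude percentage.
- **Comparisons between cohorts or with the healthy-volunteer study are undermined.** Neither AE comparison is planned. Section 11.5 and the AE item in the Protocol Summary do not split AEs by cohort.
- **The any-AE rate is badly distorted.** An acute risk of 40% with 0.2 background events per month would give 51% against 95%. But 40% lies below the 48% lower limit from Section 1.5, and at 90% the gap is about 7 points.
- **Day 30 is the shortest follow-up.** The footnotes to Table 3 allow for withdrawal before it.

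**Conclusion.** The point holds for late-onset and background events, and most clearly for individual preferred-term rows. Their reported percentages would depend on how many subjects leave for retreatment: about 5% against 45% between the extremes for a term at 0.05 per month. Acute events around dosing are largely unaffected, apart from the few subjects who may withdraw early. The any-AE figure moves little if acute AEs are as common as Section 1.5 suggests.

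The sizes rest on assumed constant rates of 0.02 to 0.20 per month, exit shares from none to all at Day 30, and an acute risk informed by only five healthy adults. The direction does not depend on those values as long as late events occur at all. With no control arm, no treatment contrast is biased; what is at risk is the reading of a descriptive table that serves a stated objective. The change should be made, but the issue does not undermine the study's ability to describe acute safety. Separately, the follow-up statement in Section 4.2 conflicts with Sections 5.4 and 9.3.

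**What to change.** In Section 11.5:

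1. Add a main AE table of events with onset from first dose to the Day 30 visit, the period over which every subject is planned to be followed, with the dosing week shown within it.
2. Report later events as events and subjects per person-month, with the number still under follow-up at each visit. State that these rates assume that exit is unrelated to AE risk, which may fail because exit depends on retreatment entry criteria.
3. Keep the all-period summary and the listing so that delayed effects stay visible, and label the summary with the range of follow-up that it covers.

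Also reconcile the 12-month minimum in Section 4.2 with the Day 30 exit in Sections 5.4 and 9.3.

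The cost is a sentence or two in Section 11.5, a wording correction in Section 4.2, and one or two extra tables. Onset dates are already collected under Section 10, so no new data are needed.

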***Sample Size and Statistical Analyses:***

The sample size of 28 subjects with LCA or RP due to RPE65 or LRAT deficiency is based on the small population of patients with these diseases and genotypes and on the clinical judgment that this is a sufficient number of subjects to meet the objectives of the study.

- AEs will be coded using the Medical Dictionary for Regulatory Activities (MedDRA) with the number and percentage of subjects experiencing an AE and the total number of events summarized by system organ class and preferred term.
- Concomitant medications will be coded with the World Health Organization Drug Dictionary and tabulated.
- Safety variables including laboratory tests, ophthalmologic examinations and procedures, and vital signs will be summarized with appropriate descriptive statistics by gene mutation subgroup, and disease cohort.
- ECG results, biomicroscopy, IOP, dilated fundus exam, height, and QLT091001 and metabolite levels (if available) will be listed by subject.
- ERG, BCVA scores measured by ETDRS testing, visual field tests, color vision, dynamic pupillometry, and nystagmus testing results will be summarized with appropriate descriptive statistics by gene mutation subgroup, and disease cohort.
- The subject questionnaire will be summarized with appropriate descriptive statistics by gene mutation subgroup, and disease cohort.

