#### **5.4 Withdrawal of Subjects**

Every effort will be made to have all subjects attend all study visits and receive all doses of study drug. Subjects can voluntarily withdraw from study treatment at any time during the study. Every effort will be made to complete study follow-up procedures if subjects terminate the study treatment early. In addition, Investigators may withdraw a subject from study treatment because:

- a new health condition appears that is suspected to require care or medications prohibited by the protocol
- the subject has unacceptable adverse events (AEs)
- the subject has clinical laboratory results as follows:
  - any hematology parameter (as listed in [Table 4](#), [Section 9.4.4](#)) that changes by more than 10% above the upper limit of the clinical laboratory value normal range
  - ALT or AST >3 times the upper limit of the clinical laboratory value normal range
  - total cholesterol, triglycerides, HDL, or LDL >2 times the upper limit of the clinical laboratory value normal range
  - thyroid function tests outside the clinical laboratory value normal range
  - serum retinol clinical laboratory value above 90 µg/dL
- the subject has a hypersensitivity reaction to study treatment (immediate withdrawal)
- the subject exhibits clinical signs of hypervitaminosis A, particularly if symptoms occur that indicate an increase in intracranial pressure (immediate withdrawal)
- there is a marked prolongation of the QT/QTc interval, such that

- it is >500 ms or increases >60 ms from baseline when the measurement obtained is averaged from the triplicate ECGs (see Section 9.4.3) (immediate withdrawal), or
  - in the Investigator's judgment an otherwise marked prolongation may indicate that the subject's safety is in jeopardy.
- it is in the subject's best interest according to the Investigator's clinical judgment

Subjects with the conditions or findings listed above will be considered for withdrawal from study treatment. Withdrawal for the reasons noted above will be reviewed in consultation with the medical monitor (refer to [Section 10.3](#)).

If a subject prematurely withdraws from study treatment, the reason(s) for withdrawal must be recorded on the relevant page of the subject's case report form (CRF).

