## 8.2 Anticipated Clinical Effects Based on Nonclinical Studies

The NOAEL in a monkey toxicology study with 28 days of dosing was 5 mg/kg or 60 mg/m^2 (most relevant species for comparison to humans). Findings at this dose were limited to changes in liver function tests that were not considered clinically significant, did not lead to any changes in treatment, and were reversible after the 28-day treatment course was completed [50].

The target organs for toxicity at the doses above the NOAEL in nonclinical studies were:

- Liver – potential effects will be monitored in this study with serum concentrations of liver enzymes and lipids.

- Bone – potential effects will be monitored in this study by monitoring serum concentrations of alkaline phosphatase and inorganic phosphate. Adverse effects on bone are considered unlikely given the short exposure period in this study.
- Heart – potential cardiac effects will be monitored in this study with ECG and vital signs.

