- e OCT Spectralis and FAF will be done at Month 2 and thereafter at the discretion of the Investigator.
- f Only if genetic testing to confirm the *LRAT* or *RPE65* mutation was not previously done by a fully accredited genotyping laboratory.
- g For women and girls of child-bearing potential, consent and Screening serum pregnancy test must be performed  $\geq 19$  days before Day -1. A serum pregnancy test will also be done on Day -1. A urine pregnancy test will be done on Day 14/15, Day 30, and Month 2. See [Section 9.4.1](#) for further details.
- h Month 2 only.
- i Blood samples collected predose on treatment days after a 12-hour overnight fast.
- j Only if clinically significant laboratory results were observed at the previous visit.
- k Includes heart rate, resting blood pressure, respiratory rate, and temperature and collected after a 3-minute resting period. Vital signs will be recorded predose and 4 hours postdose on treatment days.
- l Perform triplicate ECG recordings (3 readings in succession approximately 1 minute apart).
- m 4 hours postdose.
- n Two baseline BCVA tests will be done on separate days (Day -2, Day -1 and/or on Day 0 before treatment is given).
- o Color vision test can be done on Day -2/-1 or on Day 0 before treatment is given.
- p At the Investigator's discretion.
- q Dynamic pupillometry and nystagmus testing if appropriate instrument(s) is available.
- r Pre-dose measurement for BSA calculation for study drug dose.
- s At the last visit only: height only, measured for subjects  $\leq 19$  years of age only.
- t Dose must be calculated and study treatment prepared (see [Section 7.2](#)), before study treatment is administered.

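### ECG is planned as a by-subject listing only, so a consistent QTc change below the protocol's own limits would reach no table; late laboratory summaries also need restricting

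*Protocol*

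**What the plan says.** **ECG.** Section 11.5 fixes the analysis: "ECG, biomicroscopy, IOP, dilated fundus exam, and cycloplegic refraction results will be listed by subject". The Protocol Summary (Sample Size and Statistical Analyses) agrees: "ECG results, biomicroscopy, IOP, dilated fundus exam, height, and QLT091001 and metabolite levels (if available) will be listed by subject". By contrast, Section 11.6.2 lists drug levels but also allows a summary if data permit. ECG has no such option.

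The measurement is well specified. Section 9.4.3 averages QT/QTc over three readings at each time point. Table 3 schedules ECG for all subjects at Screening, Day -2/-1, Day 3 (4 hours postdose by footnote) and Day 7/8. Section 5.3 uses 450 ms as an example of an entry limit. For withdrawal, Section 5.4 names a QT/QTc prolongation such that "it is >500 ms or increases >60 ms from baseline when the measurement obtained is averaged from the triplicate ECGs". Section 8.2 lists the heart among the organs affected in nonclinical studies and says that "potential cardiac effects will be monitored in this study with ECG and vital signs".

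**Laboratory tests.** Table 3 schedules chemistry, hematology, thyroid and serum retinol tests for all subjects at Screening, Day -2/-1, Day 3 and Day 7/8. From Day 14/15 on, footnote j applies: "Only if clinically significant laboratory results were observed at the previous visit". Coagulation testing and urinalysis carry the same condition at Day 14/15. Section 11.5 then says: "Other safety variables including clinical laboratory test results and vital signs will be summarized with appropriate descriptive statistics". It does not separate universal from conditional visits.

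**The concern.** The protocol collects a replicated, numeric cardiac measurement on everyone and defines limits for it, then plans no group description of it. Vital signs do get descriptive statistics. A listing lets a reader check one subject at a time against a limit. It does not show whether most subjects moved a little in the same direction. The adverse-event route does not fill the gap, because only changes judged clinically significant (Section 10), or withdrawals on an ECG criterion (Section 10.4), become adverse events.

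For laboratory values the risk is a misleading summary. A subject without a clinically significant result at Day 7/8 has no further scheduled test. Any group statistic at a later visit therefore describes a few subjects chosen for a significant result, and it could be misread as describing the cohort. The adverse effects in Section 8.3 include several laboratory changes (lipids, AST, hemoglobin, red cell count), so this is where readers will look for persistence or recovery.

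**Working it through.** **The plan's own figure.** Section 11.1: 2 diseases × 2 genotypes × 7 subjects = 28. This reproduces. No alpha, power, SD or effect size is given, so the figures below illustrate precision and do not test the sample size.

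**1. What a QTc summary would give.** The SD of the within-subject QTc change is not in the documents; assume 10 to 20 ms. The half-width of the 95% CI for the mean change is t(0.975, n−1) × SD / √n.

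| n | SD 10 ms | SD 15 ms | SD 20 ms |
|---|---|---|---|
| 28 | 3.9 | 5.8 | 7.8 |
| 14 (one disease cohort) | 5.8 | 8.7 | 11.5 |

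For n = 28 and SD 20: 2.052 × 20 / 5.292 = 7.8 ms.

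**2. Would the limits alone reveal such a shift?** Take a mean shift equal to that half-width, 7.8 ms with SD 20 ms, and assume normality. The chance that one subject's increase exceeds 60 ms is P(Z > (60 − 7.8)/20) = P(Z > 2.61) ≈ 0.0045. Over 28 subjects that is about 0.13 expected exceedances. A shift the study could estimate would almost never trip the individual criterion.

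**3. What a count adds.** If no subject exceeds a limit, the one-sided 95% upper bound on the true proportion is 1 − 0.05^(1/n): 10.1% for n = 28, 19.3% for n = 14, 34.8% for n = 7.

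**4. Late laboratory values.** Assume 5% to 30% of subjects have a clinically significant Day 7/8 result (not in the documents). The expected number tested at Day 14/15 is 28 × 0.05 = 1.4 to 28 × 0.30 = 8.4. Per subgroup of 7 it is 0.35 to 2.1. The chance that at most one of 7 is tested is (1−p)^7 + 7p(1−p)^6: 96% at 5% and 33% at 30%.

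For the analyte that triggered the retest, suppose the flagged subjects are the most extreme fraction p, and values at the two visits are bivariate normal with correlation ρ. The mean of those retested is then shifted by ρ × φ(c)/p, where c is the cut-off with upper-tail probability p. The shift is in the abnormal direction, in SD units. With ρ assumed at 0.3 to 0.8:

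| p | φ(c)/p | ρ = 0.3 | ρ = 0.8 |
|---|---|---|---|
| 5% | 2.06 | 0.62 | 1.65 |
| 30% | 1.16 | 0.35 | 0.93 |

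So a shift of 0.35 to 1.65 SD can arise with no lasting drug effect. It does not carry over to unrelated analytes drawn in the same panel.

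**The case against.** **Safety is still assessed.** The objective in Section 3 is the safety of dosing for 7 days. ECGs and laboratory tests at Day 3 and Day 7/8 are scheduled for everyone, and those laboratory values are summarised without selection. Heart rate and blood pressure are summarised too. Clinically significant changes enter the adverse-event tables, and a listing of at most 28 subjects at four time points can be read against the limits. All of this stands. A reader might infer that the safety questions go unanswered; the documents do not support that.

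**The cardiac signal is qualified.** Section 8.2 says "The target organs for toxicity at the doses above the NOAEL in nonclinical studies were" before naming the heart. The monkey NOAEL it quotes is 60 mg/m², against 40 mg/m² here. This stands and limits the weight of the argument, but the same section still relies on ECG for monitoring.

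**A QTc mean is weak evidence of causation.** There is no control group, and ECGs follow institutional standards at about 6 to 7 centers. No time is set for the pretreatment ECGs to match the 4-hour postdose reading. Enrolment is up to 28, and Section 8.3 reports that 2 of the first 14 subjects received 10 mg/m². This stands: the table would describe change and could not rule out a drug-related shift.

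**Section 11.5 does not say that late laboratory values are averaged.** That is correct. It says neither mean nor by visit, and an analysis plan could restrict the visits. This keeps the laboratory point secondary. ECG differs, because the protocol itself fixes the listing.

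**Section 9.3 and footnote j.** Section 9.3 says "Visual function tests and safety assessments will be done on Day 14/15 and each subsequent visit", and a reader might infer a contradiction. There is none: Section 9.3 opens by deferring to Table 3, uses the word all only for Day 7/8, and other safety assessments do continue at later visits.

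**Conclusion.** The ECG point holds. Two places in the protocol limit the analysis to a listing, although replicated QTc is scheduled for all subjects and the protocol has its own limits. A consistent change below those limits, and not judged clinically significant in any individual, would reach no table. A summary would give a 95% interval of roughly ±3.9 to ±7.8 ms with 28 subjects and ±5.8 to ±11.5 ms with 14, on an assumed SD of 10 to 20 ms. It would be descriptive only.

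The laboratory point holds in a smaller form. Footnote j makes any group summary from Day 14/15 on a summary of a selected few: 1.4 to 8.4 of 28 expected at Day 14/15 if 5% to 30% are flagged. The possible shift of 0.35 to 1.65 SD rests on assumed flag rates and correlations, and applies only to the triggering analyte in its abnormal direction. Day 3 and Day 7/8 values are unaffected.

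Neither point means that the 7-day safety objective is unmet. The change is worth making because it uses existing data at almost no cost.

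**What to change.** **Section 11.5 and the Protocol Summary, ECG.** Keep the by-subject listing. Add a descriptive table of triplicate-averaged QTc and its change from baseline, with baseline defined as the mean of Screening and Day -2/-1, at Day 3 (4 hours postdose) and Day 7/8. Give n, mean, SD and 95% CI, with counts of subjects above 450 ms, above 500 ms and with an increase above 60 ms. These are the figures the protocol already uses. Label the table as uncontrolled and not time-matched, and identify any subjects who received a different dose.

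**Section 11.5 and the Protocol Summary, laboratory tests.** State that group summaries cover only the visits scheduled for all subjects (Screening, Day -2/-1, Day 3, Day 7/8). List later values by subject, with the number tested at each visit.

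**Cost.** A few sentences in two places, one added QTc table and a restriction on the laboratory tables. No new measurements, visits or changes to clinical rules are needed.
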